## Abstract

**Background:**

Digital methods that enable early caries identification can streamline data collection in research and optimize dental examinations for young children. Intraoral scanners are devices used for creating 3D models of teeth in dentistry and are being rapidly adopted into clinical workflows. Integrating fluorescence technology into scanner hardware can support early caries detection. However, the performance of caries detection methods using 3D models featuring color and fluorescence in primary teeth is unknown.

**Objective:**

This study aims to assess the diagnostic agreement between visual examination (VE), on-screen assessment of 3D models in approximate natural colors with and without fluorescence, and application of an automated caries scoring system to the 3D models with fluorescence for caries detection in primary teeth.

**Methods:**

The study sample will be drawn from eligible participants in a randomized controlled trial at the Royal Children’s Hospital, Melbourne, Australia, where a dental assessment was conducted, including VE using the International Caries Detection and Assessment System (ICDAS) and intraoral scan using the TRIOS 4 (3Shape TRIOS A/S). Participant clinical records will be collected, and all records meeting eligibility criteria will be subject to an on-screen assessment of 3D models by 4 dental practitioners. First, all primary tooth surfaces will be examined for caries based on 3D geometry and color, using a merged ICDAS index. Second, the on-screen assessment of 3D models will include fluorescence, where caries will be classified using a merged ICDAS index that has been modified to incorporate fluorescence criteria. After 4 weeks, all examiners will repeat the on-screen assessment for all 3D models. Finally, an automated caries scoring system will be used to classify caries on primary occlusal surfaces. The agreement in the total number of caries detected per person between methods will be assessed using a Bland-Altman analysis and intraclass correlation coefficients. At a tooth surface level, agreement between methods will be estimated using multilevel models to account for the clustering of dental data.

**Results:**

Automated caries scoring of 3D models was completed as of October 2023, with the publication of results expected by July 2024. On-screen assessment has commenced, with the expected completion of scoring and data analysis by March 2024. Results will be disseminated by the end of 2024.

**Conclusions:**

The study outcomes may inform new practices that use digital models to facilitate dental assessments. Novel approaches that enable remote dental examination without compromising the accuracy of VE have wide applications in the research environment, clinical practice, and the provision of teledentistry.

**Trial Registration:**

Australian New Zealand Clinical Trials Registry ACTRN12622001237774; https://www.anzctr.org.au/Trial/Registration/TrialReview.aspx?id=384632

**International Registered Report Identifier (IRRID):**

DERR1-10.2196/51578

## Introduction

### Background

Dental caries is the most prevalent chronic disease in childhood [1]. It causes mineral loss within the dental hard tissue, which results in visual changes in the enamel in the initial stages [2]. With increasing severity, demineralization advances into the dentine-pulp complex, and a cavity can develop [2]. More severe caries can result in pain, difficulty eating, and infection, and its management is more invasive and costly from an individual and public health perspective. In contrast, managing early caries is noninvasive, and damage to the tooth surface is reversible [3]. Epidemiological research should use methods that enable early disease detection to better target caries prevention and timely intervention programs during the early years.

### Dental Caries Detection in Epidemiological Research

In epidemiological research, visual examination (VE) is the standard method for detecting dental caries on visible tooth surfaces. VE can be subjective, particularly for early disease detection and monitoring. Validated indices, such as the International Caries Detection and Assessment System (ICDAS), improve the accuracy of VE for early caries detection [4-6]. ICDAS classifies caries based on severity, and a strong correlation exists between ICDAS and histological caries depth [7,8]. Studies using ICDAS report good inter- and intraexaminer reliability. Training and calibration improve examiner accuracy and reliability and are essential for standardizing examiners [9-11].

Epidemiological research, particularly multisite studies, requires the presence of multiple qualified dental examiners to undertake VE at the time of data collection, which is time and resource intensive. Digital photography has been suggested as an alternative to VE in these settings, where images are taken and assessed by trained and calibrated examiners. Boye et al [12] demonstrated high examiner agreement (weighted kappa, κ_w_>0.9) between VE and remote assessment of 2D images. High accuracy for caries detection has been reported using 2D images compared to a gold standard examiner; however, the threshold used for disease detection in these studies is mostly tooth cavitation. Such thresholds cannot inform and drive early disease management strategies. Novel methods that facilitate the remote assessment of dentitions without compromising accuracy relative to VE for early disease detection would have broad applications in the research setting and beyond. Intraoral scanning technology provides such a method, yet its performance for caries detection in children’s primary teeth has yet to be established.

### Intraoral Scanners for Dental Caries Detection

Intraoral scanners (IOSs) are handheld devices that create 3D digital models of the teeth and surrounding structures [13]. Digital representation of the teeth is achieved using specialized hardware (to scan the teeth) and software (to combine the data received and create 3D models). Scanners shine light onto a tooth region, and the distance between the area of interest and the scanner sensor is calculated via optical triangulation, confocal imaging, or active wave front sampling [14,15]. Numerous data points regarding tissue geometry are generated and used to construct a 3D model [14]. Red, green, and blue signals received from the tissues are applied to the model as color texture. Recently, light-induced fluorescence technology has been incorporated into the hardware of a commercially available IOS to enhance early caries detection (TRIOS 4 and 5) [16].

Light fluorescence technology is suitable for detecting and quantifying early carious lesions [17]. Exposure to blue-violet wavelength light causes sound dental tissue to auto-fluoresce green and demineralized carious dental tissue to appear darker [17]. The diagnostic capability of light fluorescence is enhanced because porphyrins, a metabolite of bacteria associated with dental caries, emit red fluorescence when exposed to light at this wavelength [18].

The interpretation of light fluorescence can be subjective, as it depends on the skill and experience of the dental practitioner. A study investigating occlusal caries detection of permanent teeth with and without fluorescence found no difference in accuracy between on-screen assessment and VE, suggesting that on-screen assessment of 3D models could be used for early caries detection and as a potential alternative to VE [19]. To our knowledge, there are no studies that have investigated the validity of on-screen assessment of 3D models for caries detection in primary teeth.

Recent advances have seen the development of computational methods as a more objective measure to quantify dental caries and support clinical diagnosis. TRIOS has developed an automated caries scoring system for their software that can automatically classify caries on occlusal surfaces based on color and fluorescence changes (TRIOS Patient Monitoring [TPM]; version 2.3; 3Shape TRIOS A/S) [16]. When comparing the diagnostic performance as quantified by the area under the curve (AUC), early in vitro and in vivo validation studies suggest that the automated score is comparable to VE at the early (AUC VE 0.71 vs 0.76) and moderate disease thresholds (AUC VE 0.90 vs 0.90), based on a histological reference standard for permanent teeth [20]. A separate investigation into the validity of this algorithm in primary teeth concluded it had comparable performance (AUC 0.88) to VE (AUC 0.96) for caries detection of primary tooth occlusal surfaces [21]. The latter was a small in vitro feasibility study; consequently, results should be interpreted cautiously and not generalized to the clinical setting. The in vivo performance of automated assessment of 3D models for caries detection in primary teeth has yet to be established.

One of the problems with investigating early caries detection methods in realistic settings is the choice of a reference standard for method comparison, as histological or operative references are rarely feasible or ethical. It is argued that when VE alone is used as a gold standard, measures of diagnostic accuracy (sensitivity and specificity) may overestimate the true accuracy of the caries detection method under investigation [22,23]. Instead, reporting on the diagnostic agreement has been suggested to be more appropriate. Diagnostic agreement quantifies the similarity between methods in detecting the outcome of interest to be used interchangeably [24].

This study describes the protocol and statistical analysis plan for determining the diagnostic agreement between VE, on-screen, and automated caries detection methods using 3D models in children.

## Methods

### Aims and Objectives

The specific study objectives are to, first, determine and compare the diagnostic agreement between VE and on-screen visual assessment of 3D models in approximate natural colors with and without fluorescence to detect and classify carious lesions on visible tooth surfaces in primary teeth. The second objective is to determine the diagnostic agreement between VE and the automated caries scoring system for detecting and classifying occlusal carious lesions in primary teeth. Finally, the third objective is to explore the impact of caries threshold, tooth surface examined (smooth vs occlusal), and enamel defects’ presence on the reported agreement estimates between caries detection methods.

### Study Design

This is a diagnostic agreement study, as VE is not considered a gold standard in this setting [23]. Dental caries in this study is defined as primary coronal caries. Data sources (age at dental visit, sex, VE data, and 3D models) will be retrospectively sourced from a sample of children who underwent VE using the ICDAS and intraoral scanning with the TRIOS 4 to produce 3D digital models.

The 3D models for each eligible participant will be subject to an on-screen assessment by 4 qualified dental practitioners. Each practitioner will examine all 3D models at 2 separate time points. An on-screen assessment of 3D models based on tissue geometry and approximate natural colors (excitation to visible white light) will take place first (Figure 1A), followed by an on-screen assessment with the addition of fluorescence texture (excitation to light at 415 nm; Figure 1B). An interval of at least 4 weeks will follow to minimize recall bias before the on-screen assessment process is replicated. Occlusal surfaces of primary molars will be examined using the automated caries scoring system at a single time point only (Figure 1C). Examiners will be blinded to all clinical examination data and automated caries scores when scoring the 3D scans.

**Figure 1 figure1:**
[figure not shown]
Caries detection methods based on 3D models obtained using an intraoral scanner.

### Study Setting and Participants

The study sample will be drawn from eligible participants in an existing randomized controlled trial, the Melbourne Infant Study Bacille Calmette Guérin (BCG) for Allergy & Infection Reduction (MISBAIR; ClinicalTrials.gov NCT01906853; for a complete description of the trial, please refer to the MISBAIR study protocol) [25]. English-speaking immunocompetent pregnant women scheduled for birth at hospitals servicing Werribee, Ballarat, Geelong, and Melbourne in Victoria, Australia, from mid-2013 to mid- to late 2016 provided consent for their infants to participate in a longitudinal and randomized controlled trial to determine if BCG immunization within the first 10 days of life prevents the development of allergy and infection in early childhood. Infants were excluded if they had any conditions at birth that would contraindicate the use of live vaccines. The MISBAIR trial included a 5-year-old study visit where a clinical assessment (including dental assessment) was undertaken (219/536, 40.9% remaining MISBAIR participants). All study visits occurred between January 31, 2021, and March 31, 2022, at the Murdoch Children’s Research Institute in Melbourne.

### Participant Eligibility Criteria

MISBAIR participant data will be included for analysis in this study if participants meet the following criteria: (1) attended the 5-year-old study visit for MISBAIR (target age 4-6 years), (2) completed of a VE during the 5-year-old study visit, (3) acquired an intraoral scan at the same time as the VE, and (4) provided informed consent for the analysis of dental data and on-screen assessment of 3D models.

### Tooth Surface Inclusion Criteria

For each participant, a tooth surface will be eligible for on-screen assessment if it (1) has been examined as part of the dental exam, (2) is from a primary tooth, and (3) is visible on the 3D model.

### Tooth Surface Exclusion Criteria

Tooth surfaces will be excluded from on-screen assessment if (1) they have a sealant, direct or indirect restoration; (2) the tooth surface visibility on the 3D model is impeded by calculus, debris, or plaque; and (3) less than one-third of the surface is visible due to insufficient or missing scan data.

Tooth surfaces will be excluded from the application of the automated caries scoring system if they (1) have a sealant, direct or indirect restoration; (2) have an enamel defect; (3) are not a primary molar occlusal surface; and (4) less than one-third of the surface is visible due to insufficient or missing scan data.

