### Dental Examination Protocol at the 5-Year-Old Study Visit

#### VE Protocol

VEs occurred with participants in a semisupine position on an adjustable examination bed. The examiner stood to the side of, or behind, the participant. A portable LED light (220 lumens NÄVLINGE clamp spotlight IKEA) and a dental mirror were used and positioned to provide maximum illumination and visibility of the oral cavity without magnification. Cotton rolls and swabs were used to dry teeth and remove plaque. Compressed air was not used. Universal infection control standards and additional COVID-19 precautions were adhered to for all examinations.

Dental examinations were conducted by trained and calibrated registered dental practitioners (BJ and [name]) with experience and prior training in using the ICDAS index in research settings. Examiner BJ is an oral health therapist with 13 years of clinical experience, and examiner [name] is an oral health therapist with 5 years of clinical experience. Before commencing VEs, both examiners had participated in the web-based ICDAS and International Caries Classification and Management System (ICCMS) e-learning modules [26]. Additionally, a senior researcher and pediatric dentist (MS) with experience in conducting surveys using ICDAS and enamel defect indices facilitated a presentation on ICDAS using the ICDAS or ICCMS examiner training materials and training materials for the use of a modified molar incisor hypomineralization (MIH) index to assess for enamel defects (with permission from the author) [27]. A 2-hour calibration session on the application and interpretation of the indices, followed by a computer-based calibration exercise, took place. The computer-based calibration exercises were repeated until both examiners reached an intra- and interexaminer agreement of κ_w_>0.8.

Dental caries experience was recorded for each tooth surface using the 2-digit ICDAS criteria [28]. Code 01 could not be scored for smooth surfaces due to a lack of compressed air. Enamel defects were recorded using a modified MIH index describing each surface’s clinical presentation and the extent of the defect [29]. All tooth surfaces were examined using a systematic approach. The score given was the most severe of the 2 clinical presentations if multiple lesions were present on the same tooth’s surface.

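### Automated scoring and on-screen reading use different surface exclusions, in both directions, and the pairwise lesion counts are not tied to a common set of surfaces

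*Protocol article*

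**What the plan says.** Under Tooth Surface Exclusion Criteria, the protocol article gives two separate lists. For on-screen reading, a surface is removed if it is sealed or restored, if "the tooth surface visibility on the 3D model is impeded by calculus, debris, or plaque", or if too little of it was captured. The second list opens: "Tooth surfaces will be excluded from the application of the automated caries scoring system if they (1) have a sealant, direct or indirect restoration". It continues: "2) have an enamel defect; (3) are not a primary molar occlusal surface; and (4) less than one-third of the surface is visible". Plaque, calculus and debris do not appear in it, and enamel defects do not appear in the first list.

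The VE Protocol records that "Cotton rolls and swabs were used to dry teeth and remove plaque". The Intraoral Scanning section says the scan came straight after VE, with the teeth dried again beforehand. The Introduction says that porphyrins produced by caries-associated bacteria "emit red fluorescence when exposed to light at this wavelength". It also says that the automated score uses colour and fluorescence change, and the Automated Caries Scoring System section says regions are judged against a healthy reference on the same tooth.

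In Statistical Analysis, the individual-level outcome is the number of lesions per child. The Bland-Altman regression and the intraclass correlation are both to be run for every pairing of methods. No restriction to shared surfaces is stated.

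**The concern.** A lesion count can be compared between two methods only if both had the same surfaces on which to find lesions. Here a plaque-obscured molar surface can add to the automated count but not to the on-screen count. A molar surface with an enamel defect can add to the on-screen count but not to the automated count. The automated versus on-screen analyses would then mix two things: disagreement about caries, and a difference in what was counted.

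The automated versus VE comparison, which is the second study objective, raises a narrower question. It keeps any surface that the protocol considers too obscured to read from the same 3D model. Disagreement with VE on such a surface cannot be separated into a misjudged lesion and an obscured scan.

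**Working it through.** **1. The two lists side by side**

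| Reason | On-screen reading | Automated scoring |
|---|---|---|
| Sealant or restoration | removed | removed |
| Obscured by plaque, calculus or debris | removed | kept |
| Enamel defect | kept | removed |
| Too little captured (scan data missing) | removed | removed |
| Not a primary molar occlusal surface | kept if primary and visible | removed |

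The automated list repeats the two shared items, so it reads as complete and not as an addition to the first list.

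**2. Does another rule close the gap?** The visibility item common to both lists applies where "less than one-third of the surface is visible due to insufficient or missing scan data". A well-captured surface covered by plaque does not meet it. The inclusion criteria do not help, because they are written for one method: "a tooth surface will be eligible for on-screen assessment if it (1) has been examined as part of the dental exam".

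**3. Effect on automated versus on-screen counts.** Take one child's primary molar occlusal surfaces. Let A be those eligible for automated scoring and S those eligible for on-screen reading, with a and s the 0/1 caries calls. The count difference is

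D = Σ over A∩S of (a − s) + Σ over A-only of a − Σ over S-only of s.

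Only the first term measures agreement. A-only holds plaque-obscured surfaces without a defect; S-only holds defect surfaces that are not obscured. As a hypothetical example, take 8 molar occlusal surfaces, one of each kind, and perfect agreement on the other 8 − 1 − 1 = 6. Then D = 0 + a − s, which can be −1, 0 or +1 although the methods never disagree on a shared surface. This step needs no assumption about how plaque fluoresces.

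**4. Effect on automated versus VE.** Only the plaque, calculus and debris item matters here. The documents support three statements: the score depends on fluorescence; certain bacterial products fluoresce at the scanner's wavelength; and the on-screen rule provides for obscured surfaces on these models. Together they make an altered score possible. They do not say how often it occurs or in which direction.

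**5. Size.** The article gives no figure to reproduce. It reports automated scoring in 213 participants. Assuming 8 primary molars each, there are at most 213 × 8 = 1,704 surfaces before exclusions. Let q be the share with residual plaque and f the share of those whose automated call becomes wrong against VE. Both are assumptions with no anchor in the article.

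- q = 2%, f = 25%: q × f = 0.5 percentage points of agreement; 1,704 × 0.005 ≈ 9 surfaces; 8 × 0.005 = 0.04 per child.
- q = 10%, f = 75%: q × f = 7.5 percentage points; 1,704 × 0.075 ≈ 128 surfaces; 8 × 0.075 = 0.60 per child.

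The fifteenfold spread comes entirely from the assumed inputs. The calculation also supposes that every altered call creates a disagreement, so at given inputs it shows the adverse case.

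**The case against.** The strongest reply is that plaque was removed at VE and the scan followed at once, so only residual material is at issue. This stands, and it probably keeps the affected surfaces few. It does not remove the point: the authors still wrote an exclusion for obscured surfaces on these models, and the enamel-defect mismatch does not depend on plaque.

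Second, keeping plaque-affected surfaces may be deliberate, because it estimates agreement under conditions the software would meet in use. That is a legitimate target, and dropping those surfaces could flatter the tool. The planned automated versus VE analysis should therefore stay, with the restricted one beside it.

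Third, on-screen reading covers all visible primary surfaces and automated scoring only molar occlusal ones. That gap is far larger than any plaque difference, and analysts would presumably restrict to molar occlusal surfaces. Doing so removes the larger mismatch but leaves both items in step 3. The common set might be defined in a fuller analysis plan; however, the article states both lists in full, and they conflict with a like-for-like count.

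Fourth, enamel defects enter the planned regression models. They do so only in the surface-level analyses and as a per-child variable, so they do not correct the individual-level counts.

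A reader might also infer that plaque makes the software over-call caries, inflating its counts and lowering its agreement with VE. The documents do not support that. The Introduction ties red fluorescence to caries-associated bacteria and does not say that plaque on sound enamel fluoresces or is flagged. Plaque might equally mask a lesion or disturb the tooth's healthy reference.

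**Conclusion.** The two exclusion lists differ in both directions, and the plan compares lesion counts for every pair of methods without a common surface set. Automated versus on-screen differences will therefore partly reflect different surface sets. Automated versus VE agreement will include any surfaces the protocol treats as unreadable on the same models. The first conclusion follows from the text alone. The importance of the second depends on how much plaque remained after cleaning and how the software responds to it, and the article gives neither.

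The effect of plaque is probably small, and its direction and size cannot be determined. The illustrative 0.5 to 7.5 percentage points only show how the result moves with the inputs. A figure for spurious automated lesions per child should not be read as an estimate. This is a gap worth closing, not a flaw that invalidates the study.

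**What to change.** For every automated versus on-screen comparison, count lesions only on primary molar occlusal surfaces eligible under both lists.

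For automated versus VE, keep the analysis of all surfaces eligible for automated scoring, with VE counted on those same surfaces. Add a sensitivity analysis that leaves out surfaces excluded on screen for plaque, calculus or debris.

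Prespecify how exclusions are combined across the four readers and two readings, since they may differ. One option is exclusion by a majority at the first reading, meaning at least three of four, so that a two-two split keeps the surface. Confirm that readers record the reason for each exclusion; the article does not say so, and the sensitivity analysis needs it.

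This is a cheap improvement: a filter on eligibility decisions already being made and a repeat of the automated analysis, with no rescanning or rescoring. The costs are fewer surfaces in the restricted set and a wait for on-screen reading, expected to finish in March 2024. The Abstract expects the automated results to be published by July 2024, and the Results section within six months of October 2023. The second date would leave little time, so the sensitivity analysis might have to follow the first report.
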